## 3. Study Objectives and Endpoints

### 3.1. Primary Objective and Endpoints 

The primary objective is to demonstrate that the application of the 4PEPS strategy by the emergency physicians in comparison to current practices (i) does not increase the risk of serious events related to diagnostic strategies and (ii) significantly reduces the use of thoracic imaging. 

The primary safety endpoint will be the rate of serious events in the 90 days following inclusion:Serious adverse events related to diagnostic testing (leading to hospitalization or prolongation of hospitalization, permanent inability or incapacity, and death).Symptomatic thromboembolic events in patients not diagnosed with PE in the emergency department or new thromboembolic events in patients diagnosed with PE.Death related to PE (initial or recurrent PE).Major bleeding related to the anticoagulant treatment prescribed for pulmonary embolism according to ISTH criteria [21].

All events must be symptomatic, documented, and confirmed by the clinical adjudication committee blinded to the study group. For analysis of deaths in cases where an autopsy is not performed, a precise definition of the elements indicating that the death is possibly related to pulmonary embolism will be used according to recent ISTH proposals [22].

The primary efficacy endpoint will be the rate of thoracic imaging among all included patients with suspected PE. A relative reduction of at least 20% is expected.

The following thoracic examinations will be considered if they are performed at the request of the emergency physician in search of PE and this during the passage in the emergency department and/or within 72 h of inclusion:CTPA.Planar perfusion or perfusion–ventilation pulmonary scintigraphy.SPECT scintigraphy.

The examinations have to be mentioned in the patient’s record and be the subject of a report, with analysis of the file taken as proof of this. 

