## 9. Statistical Analysis

### 9.1. General Considerations 

Population characteristics will be described using their mean/standard deviation, median/interquartile range, or percent/95% confidence interval, as appropriate. Univariate comparisons will be made using Student’s, Mann–Whitney, or Fisher’s exact tests, as appropriate. The alpha risk will be set at 5%. All tests will be one-sided. Given that some proportions are expected to be small, confidence intervals will be calculated using the Clopper and Pearson exact method. 

The analysis will be performed using R software (R Foundation for Statistical Computing; 2008. http://www.R-project.org (accessed on 1 November 2022)) and its PropCIs and MASS add-ons (http://CRAN.R-project.org/package=PropCIs (accessed on 1 November 2022)). All objectives will be analyzed on the overall included population (intention-to-treat). A complementary per-protocol analysis will be performed, especially for the 4PEPS strategy in the interventional group. 

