### 9.2. Primary Statistical Analysis

The two main endpoints will be analyzed in a hierarchical manner. Firstly, non-inferiority will be analyzed on the safety endpoint with a non-inferiority limit set at 1.5%. If and only if confirmed, superiority analysis on the efficacy endpoint will be performed. Analyses will be performed using a mixed-effects logistic regression in line with recommendations for this type of study [26]. Missing data will be analyzed in order to determine whether they are informative and whether they are likely to cause a potential screening or information bias. 

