### 10.1. Safety Endpoint

Considering the participation of 20 centers, 10 centers in each group, an alpha risk of 5%, a power of 80%, a clinical event rate of 1.5% at 3 months in both groups, a non-inferiority limit of 1.5%, an intra-center correlation coefficient of 0.002, and a rate of patients lost to follow-up or non-analyzable of 5%, it will be necessary to enroll 2560 patients, 1280 in each arm.

The serious clinical event rate at 3 months will be estimated by taking into account a risk of adverse event related to diagnostic testing of 0.1%; a PE prevalence of 14% [10,11]; a risk of thromboembolic events in patients for whom the diagnosis is ruled out estimated at 0.8% [15] and in patients for whom the diagnosis is made (14% of the population); a PE-related death rate of 2% [28,29]; major bleeding of 2% [28]; and thromboembolic recurrence of 2% [29]. The intra-center correlation rate at 0.002 and the non-inferiority limit at 1.5% will be estimated on the basis of a recent French study [30].

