### 10.2. Efficacy Endpoint 

Considering the participation of 20 centers, an alpha risk of 5%, a power of 80%, an intra-center correlation coefficient of 0.05, and a usage rate of thoracic imaging of 45% in the control group, it will be necessary to include 2128 patients to demonstrate a relative decrease (1-sided analysis) greater than or equal to 20% (an absolute decrease of 9%) between the control and interventional groups in the usage rate of thoracic imaging. 

The intra-center correlation coefficient will be set at 0.05, given that the use of imaging is strongly linked to professional practices, which themselves vary significantly between centers. We estimate that it will be 45% in the control group and 36% in the interventional group on the basis of a previous retrospective assessment [15].

This means the figures previously calculated (2560 patients) will be sufficient for the hierarchical analysis of this endpoint. Nevertheless, an analysis of the usage rate of thoracic imaging in the control group will be performed after the inclusion of 1500 patients, i.e., 750 patients in the control group. If this rate is lower than expected (<45%), a reassessment of the sample size will be performed in order to assure a power of 80% to demonstrate a relative decrease of at least 20% between the control and the interventional groups on the usage rate of thoracic imaging.

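### Section 10.2 calls 2560 patients sufficient for the hierarchical imaging analysis, but its 80% is the stand-alone power of a test that runs only if the safety gate is passed

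*Protocol article*

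**What the plan says.** Section 3.1 states one primary objective with two parts, to show that the 4PEPS strategy "i) does not increase the risk of serious events related to diagnostic strategies and (ii) significantly reduces the use of thoracic imaging". Section 9.2 puts them in a fixed order, safety non-inferiority (limit 1.5%) and then imaging: "If and only if confirmed, superiority analysis on the efficacy endpoint will be performed". Section 9.1 sets alpha at 5% and adds "All tests will be one-sided".

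Section 10.1 sizes the safety test alone, with 20 centers, "an alpha risk of 5%, a power of 80%, a clinical event rate of 1.5% at 3 months in both groups", an intra-center correlation (ICC) of 0.002 and 5% loss, and arrives at 2560 patients (1280 per arm). Section 10.2 sizes the imaging test alone, with 80% power, ICC 0.05 and 45% versus 36%, and arrives at 2128. It then says: "This means the figures previously calculated (2560 patients) will be sufficient for the hierarchical analysis of this endpoint".

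Section 10.2 also plans a reassessment after 1500 patients. If control-arm imaging is below 45%, the sample size is revisited to secure 80% power for the imaging comparison.

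**The concern.** Taking the larger of two stand-alone sample sizes secures the planned power for each test separately. It does not secure it for a test that is reached only through another. The fixed sequence protects the type I error, as the Discussion says, but it costs power at the second step, and the article does not count that cost.

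The primary objective is met only if both tests succeed. A reader of 10.2 would take it that a true 20% relative reduction in imaging, with equal safety, is missed about one time in five. Under the written rule it is missed more often, partly because in some trials the safety test fails by chance and imaging is never formally tested. The reassessment is the point at which the sample size can still move, and it looks at the imaging test alone, so it would carry the same omission forward.

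**Working it through.** **Inputs.** Order of testing: 9.2. One-sided 5%: 9.1. Safety rate 1.5% in both arms, margin 1.5%, ICC 0.002, 5% loss, 1280 per arm: 10.1. Imaging 45% versus 36%, ICC 0.05, N = 2128: 10.2. Ten centers per arm: section 5. The article gives no correlation between the two test statistics, so the values used below are assumptions.

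**1. The stated sample sizes.**
- *Safety.* At one-sided 5% the unclustered requirement is 812 per arm. With ICC 0.002, 10 centers per arm and 5% loss, the total is about 2037, not 2560. A total near 2560 appears only at one-sided 2.5% with the loss left out (about 2586-2592).
- *Imaging.* At one-sided 5% the unclustered requirement is 367 per arm. With 10 centers per arm and ICC 0.05 the effective size per arm cannot exceed 10/0.05 = 200, so no N reaches 80% (ceiling 57.5%). The figure 2128 (1064 per arm, 106.4 per center) implies ICC = (1064/367 - 1)/(106.4 - 1) = 0.018.

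Neither figure is reproduced from its stated inputs. The gate question is therefore worked on three bases.

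**2. Both printed powers accepted.** Power through the gate is P(safety passes and imaging significant).
- Independence: 0.80 x 0.80 = 0.64.
- Bivariate normal test statistics with correlation -0.3, 0.3, 0.5: 0.62, 0.67, 0.69.
- Logical bounds: 0.80 + 0.80 - 1 = 0.60 up to min(0.80, 0.80) = 0.80. The upper bound needs both tests to succeed in exactly the same trials.

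**3. Surplus credited.**
- *Safety.* Analysable per arm = 1280 x 0.95 = 1216, or 121.6 per center. Design effect = 1 + 120.6 x 0.002 = 1.2412. SE = sqrt(2 x 0.015 x 0.985 x 1.2412/1216) = 0.00549. Power = Phi(0.015/0.00549 - 1.645) = Phi(1.086) = 0.861.
- *Imaging.* If 2128 did give 80% (ICC 0.018), 1280 per arm has design effect 1 + 127 x 0.018 = 3.29, effective size about 389 and power 0.82.
- Joint, under independence: 0.80 x 0.82 = 0.656 to 0.861 x 0.82 = 0.706.
- Chance that imaging is never tested: 1 - 0.861 = 14% to 1 - 0.80 = 20%.

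**4. Printed ICC of 0.05.** At 1280 per arm the design effect is 1 + 127 x 0.05 = 7.35 and the effective size 1280/7.35 = 174. Imaging power is about 0.53 (about 0.50 with a t reference on 18 df). Joint, under independence: 0.80 x 0.53 = 0.424 to 0.861 x 0.53 = 0.456. It cannot exceed 0.53 at any correlation.

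| Basis | Safety | Imaging | Joint (independent) |
|---|---|---|---|
| Printed powers | 80% | 80% | 64% |
| Surplus credited | 80-86% | 82% | 66-71% |
| Printed ICC 0.05 | 80-86% | 53% | 42-46% |

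**The case against.** The strongest reply is that nothing printed is false. Each 80% is attached to its own test, no joint power is claimed, and quoting power per endpoint in a fixed sequence is a legitimate reporting choice. The sentence in 10.2 can be read to mean only that the N fixed by the first test also covers the second. It is true that no 80% joint power is printed, and a reader who infers that the article claims one goes beyond the text. But the sentence speaks of the hierarchical analysis, and for that analysis a comparison of 2560 with 2128 settles nothing. The statement as made does not follow.

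Three further points stand and limit the concern.
- A reader might infer that both printed powers are wrong under the hierarchy. They are not: safety is tested first and ungated, so 10.1 needs no change on this ground.
- A reader might take 64-71% as the power on the plan's own inputs. It is not. It accepts an imaging power of 80%, or an ICC of 0.018 that the article never states. The printed ICC of 0.05 gives 42-46%.
- The simple product assumes independence, which the article does not state. The correlation range and bounds belong beside any such figure.

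The mismatch between ICC 0.05 and 2128 is a separate and larger problem: it takes about 27 points from imaging power (80% to 53%), against at most 20 for the gate when both powers are 80%. Correcting it would change the marginal powers but would not remove the gate. Any increase in N at the reassessment would also raise safety power; that softens the omission there without closing it.

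**Conclusion.** The point holds in a limited form. The sufficiency statement in 10.2 is unsupported because the 80% behind it is a stand-alone power for a gated test. If both stated powers are accepted and the tests are roughly independent, the shortfall against 80% is about 16 points, or about 9 to 14 points with the surplus credited. A true effect with equal safety would then be missed in about 29-36% of trials instead of 20%. On the printed ICC the shortfall is about 34 to 38 points, most of it due to the ICC and not the gate. All these figures assume true rates equal to the planning values. The direction does not depend on the correlation, except in the limiting case where one test's success implies the other's.

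The documents do not support the conclusions that the type I error is compromised, that the safety power is misstated because of the hierarchy, or that more patients must be recruited on this ground. Whether to power the conjunction is a planning choice; describing the present power correctly is not.

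**What to change.** In 10.2, replace the sufficiency sentence with a statement that 80% is the marginal power of each test. Report the power of the imaging test through the safety gate, with the assumed correlation between the two test statistics and the range over plausible correlations. Compute it after the efficacy inputs (ICC 0.05 with 10 centers per arm, and N = 2128) have been reconciled; until then any single joint figure is provisional. In the reassessment after 1500 patients, report power through the gate alongside the imaging test's own power.

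This is a change of wording plus one calculation. Design, test order and number of patients stay as they are. The cost is a less favourable stated power.

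### At the stated ICC of 0.05 with 20 centres, the interim sample-size reassessment for imaging cannot secure 80% power by adding patients

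*Protocol article*

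**What the plan says.** Section 10.2 of the protocol article sizes the imaging endpoint for 20 centres with "an alpha risk of 5%, a power of 80%, an intra-center correlation coefficient of 0.05". It gives the rates as follows: "We estimate that it will be 45% in the control group and 36% in the interventional group". The resulting total is 2128, so the 2560 patients required for safety (Section 10.1) are taken to be enough.

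The section then adds a safeguard: "an analysis of the usage rate of thoracic imaging in the control group will be performed after the inclusion of 1500 patients", that is, 750 control patients. The action follows: "If this rate is lower than expected (<45%), a reassessment of the sample size will be performed". Its declared purpose is to guarantee 80% power against a relative reduction of one fifth or more. The only quantity named as input to the trigger is the control imaging rate. On the other main parameter the text says "The intra-center correlation coefficient will be set at 0.05", because imaging practice differs considerably between centres. Sections 4.1 and 5 give 20 centres, 10 per arm. Section 9.1 states: "All tests will be one-sided".

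**The concern.** In a cluster trial with a fixed number of centres, extra patients per centre reduce only the within-centre part of the variance. The between-centre part remains, and it sets a ceiling on power. If that ceiling is below 80% at the planning values, it is lower still when the control rate falls, because a 20% relative reduction is then a smaller absolute difference. The rule is meant to act in exactly that situation.

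The sponsor could then recruit many more patients for almost no gain, or adopt a new total labelled as 80% power that does not have it. A control rate at or above 45% would trigger nothing, even if the ICC left the second primary endpoint badly underpowered.

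**Working it through.** **Inputs.** Section 10.2: 45% vs 36%, ICC 0.05, power 80%, alpha 5% one-sided, look at 750 control patients. Section 5: k = 10 centres per arm. Section 10.1: 2560 patients, so m = 128 per centre. For a lower control rate I keep the 20% relative reduction, for example 40% vs 32%.

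**1. The plan's own figure.**
- Independent patients per arm for 45% vs 36%: 365 (unpooled variance) or 367 (pooled).
- At 2128 patients, m = 2128/20 = 106.4 and the design effect is 1 + 105.4 × 0.05 = 6.27. The total is 2 × 367 × 6.27 ≈ 4602, not 2128. At 106.4 patients per centre, 4602 patients would need about 22 centres per arm.
- The formula with k fixed, n = k·n_ind·(1 − ICC)/(k − n_ind·ICC), has denominator 10 − 367 × 0.05 = 10 − 18.35, which is negative. There is no solution.
- 2128 is obtained if the ICC is about 0.018: (1064/367 − 1)/105.4 = 0.018.

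**2. Ceiling with 10 centres per arm.** The effective size per arm is k·m/[1 + (m − 1)·ICC], which tends to k/ICC = 10/0.05 = 200 as m grows. The requirement is 365 at 45% vs 36%, 442 at 40% vs 32% and 541 at 35% vs 28%.

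**3. Power.** Power = Φ(Δ/SE − 1.645), with SE² = [p1(1 − p1) + p2(1 − p2)]·[1 + (m − 1)·ICC]/(k·m).

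Example, 45% vs 36% at 2560: SE² = 0.4779 × 7.35/1280, SE = 0.0524, Δ/SE = 1.718, power 53%. With unlimited patients: SE² = 0.4779 × 0.05/10, SE = 0.0489, Δ/SE = 1.841, power 58%.

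| Control vs intervention | 2560 patients | 5000 patients | Unlimited patients |
|---|---|---|---|
| 45% vs 36% | 53% | 55% | 58% |
| 40% vs 32% | 47% | 49% | 51% |
| 35% vs 28% | 41% | 43% | 45% |

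A t reference with 18 degrees of freedom lowers these by about 2 to 3 points (50% at 2560 and 55% at the ceiling for 45% vs 36%).

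**4. Dependence on the ICC.** At 2560 patients and 45% vs 36%, power is about 82% at ICC 0.018, 80% at 0.02, 74% at 0.025 and 53% at 0.05. With unlimited patients in 10 centres per arm, 80% needs an ICC below 10/365 ≈ 0.027. At a 40% control rate the limit is 10/442 ≈ 0.023.

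**5. Centres needed at ICC 0.05.** The minimum per arm with unlimited patients is n_ind × ICC: 18.2 to 18.35 at 45%, so at least 19, and 22.1 at 40%, so at least 23. With 128 patients per centre it is 365 × 7.35/128 ≈ 21 (22 with pooled variance) at 45% and 442 × 7.35/128 ≈ 26 at 40%.

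**6. Trigger.** With 75 patients in each of 10 control centres the design effect is 1 + 74 × 0.05 = 4.7 and SE = √(0.45 × 0.55 × 4.7/750) = 0.039. Because the threshold equals the planning value, the look falls below it about 50% of the time when 45% is true. If the 10 centres are regarded as a draw from a wider population, it also does so about 10% of the time when the true rate is 50%.

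**The case against.** **The fault lies upstream.** The 2128 total does not agree with ICC 0.05 and 20 centres, and the reassessment inherits that error. This stands as a description of the cause. Correcting 2128 alone, however, would leave a rule that still promises 80% power on the basis of the control rate.

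**The text does not limit the reassessment to patients.** Sample size in a cluster trial can include centres, and a condensed article may leave re-estimation details to the full protocol. A reader might therefore infer that no design could reach 80%, or that the ICC will never be examined. The article supports neither: it does not exclude more centres (about 21 or 22 per arm of 128 patients would suffice at 45%), and its silence about the ICC is not a refusal to estimate it. What it does state is 20 centres, ICC 0.05, a trigger on the control rate alone and assurance of 80%. These do not fit together.

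**The trigger.** A reader might also infer that chance will decide whether recruitment is extended. That goes too far. A rate below 45% starts a recalculation, not an extension. On the protocol's own accounting there is slack: at the ICC that returns 2128 (0.018), a 44% control rate needs 381 independent patients per arm, hence 20 × 381 × 0.982/(10 − 6.858) ≈ 2380 in total, still below 2560. The 3.9-point SE also ignores stratification on baseline imaging rate (Section 5). For the particular centres in the trial, the SE is √(0.45 × 0.55/750) = 1.8 points. The 50% trigger frequency is therefore a minor point.

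**The true ICC may be lower**, perhaps helped by stratification. That is possible, but the protocol takes no credit for it and plans with 0.05. It is a reason to estimate the ICC at the look.

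**Conclusion.** The point holds in a limited form. With 20 centres, ICC 0.05 and one-sided 5%, adding patients cannot secure 80% power at a control rate of 45% or below. At 45% vs 36% power is about 53% at 2560 and at most 58%; at 40% vs 32% it is about 47% and at most 51%. Doubling recruitment to about 5000 gains some 2 points.

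This rests on the number of centres staying at 20, equal centre sizes, a normal approximation (a t reference is slightly worse) and the protocol's own ICC. It would not hold if centres were added, or if the ICC were below about 0.027 and enough patients were recruited (about 0.02 at the planned 2560). Severity: should-fix, linked to the inconsistency between 2128, ICC 0.05 and 20 centres.

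**What to change.** Amend Section 10.2, together with the 2128 figure:

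- At the 1500-patient look, estimate the control-arm imaging rate and the within-arm ICC, without comparing the arms. The rate should not be pooled across arms, because that mixes in the treatment effect. Nor should the ICC ignore arm: at 45% vs 36% the arm difference alone would add about 0.045²/(0.405 × 0.595) ≈ 0.008.
- Use the pre-randomisation survey of imaging rates in the participating centres (Section 5) to support the ICC estimate, since 10 centres per arm give an imprecise one.
- Compute attainable power with a formula that holds the number of centres fixed.
- Replace the assurance of 80% with a statement of attainable power. Extend patient recruitment only if 80% is reachable in the existing centres at the estimated ICC; otherwise keep 2560 and restate the power.

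The cost is wording and one small additional analysis. The abstract gives the trial as not started, so the change is cheap now. The downside is that the sponsor may have to report power well below 80% for the efficacy endpoint.

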## 11. Funding, Ethical Considerations, and Regulations

This work will be funded by a French Public Health grant (PREPS-N 2019) and will be sponsored by the University Hospital of Angers. The funding source and the sponsor will play no role in the study design, data collection, analysis, interpretation, or the writing of the manuscript.

The study file (including the protocol, the summary, the list of associated researchers and the study information letter) will be submitted for approval to the ethics committee (CPP). The study will be only initiated after a favorable opinion for conducting this research.

Informed consent will be obtained for all patients and an information letter will be provided to all participants. The data relating to this study will be processed in accordance with the EU General Data Protection Regulation and the study sponsor will sign an agreement to comply with the “Reference Methodology” (declaration number: 1174822). 

The results of the study will be published in peer-reviewed journals and will be presented at conferences.

## 12. Discussion 

The 4PEPS score was specifically derived to reduce over-testing for PE suspicion using a Bayesian approach. The 4PEPS strategy compared well retrospectively with other strategies but required a formal validation in a prospective trial. SPEED&PEPS will provide this unmet need with a very high level of evidence. Analysis of the rate of thromboembolic events occurring in the 3 months of follow-up in patients considered free of PE and not treated with anticoagulant therapy is the most used method for assessing the diagnostic reliability of a diagnostic exclusion strategy for suspected PE, reflecting the false-negative rate of that strategy [8,9,10,11,12,13,14]. The false-negative rate and its 95% CI are compared to a predetermined cut-off, ideally, that defined according to ISTH recommendations [16]. In SPEED&PEPS, this analysis will be carried out but at a complementary element of the analyses of the overall net clinical benefit and efficacy of the 4PEPS strategy as compared with usual practices.

To assess the effects of an intervention on practice, cluster-randomized controlled studies are considered the most relevant, but they require particular analysis [19,20,31]. In such studies, randomization is carried out by the center, but efficacy is judged at the patient level, which increases the number of subjects to include in order to demonstrate an effect and determines the type of statistical tests to be used [26,32,33,34]. Randomizing patients individually would entail a risk of contaminating the strategies between them [35]. The pragmatic design of SPEED&PEPS will help reconcile healthcare-related organizational constraints and the demands of a rigorous scientific evaluation, and it will be particularly tailored to emergency departments [23,27,30]. To ensure that patients are managed according to good medical practice throughout the study, the physicians will be reminded of relevant recommendations and will have the possibility to use the clinical help–decision support software SPEED. SPEED has been shown to improve the diagnostic management of suspected PE in a prospective randomized multi-center study that compared SPEED to the wide distribution of recommendations in paper form [23].

As part of a de-escalation approach, aimed at limiting the overuse of diagnostic testing, analysis of the efficacy on high-risk and/or costly diagnostic investigations (in this case, CTPA or scintigraphy) must be combined with a safety analysis to ensure that the reduction in investigations is not linked to an increase in the number of serious clinical events related to the diagnostic approach. By drawing on Bayesian principles, the diagnostic approach seeks to make a diagnostic and therapeutic decision that either: (1) makes the diagnosis and initiates anticoagulant treatment when the risks associated with the treatment—mainly serious hemorrhages—are lower than the benefits it may provide on the progression of the disease, mainly in terms of mortality and thromboembolic recurrence; or (2) does not make a diagnosis and does not initiate anticoagulant therapy when the risk of progressive thromboembolic pathology, still in terms of mortality or thromboembolic recurrence, is less than the risk of therapeutic side effects [36]. Thus, in addition to severe adverse events directly related to investigations, the progression of PE to death or the occurrence of a new thromboembolic event (therapeutic defect or failure) and the occurrence of a serious hemorrhage (side effect of anticoagulant therapy) are serious clinical events related to the diagnostic strategy. The overall rate of serious clinical events occurring during follow-up reflects the net clinical benefit of the diagnostic approach and the resulting therapeutic decision. It is assessed on all included patients with suspected PE and can be used as a basis for medico-economic analysis.

The hierarchical analysis applied in SPEED&PEPS will allow us to address the questions of efficacy and safety without increasing the alpha risk through multiple tests. If our research hypothesis is confirmed, this will have a major impact for patients and for public health. For patients, the reduction in the use of imaging tests will make it possible to limit the cumulative radiation exposure, the impact of which is now known in terms of the risk of radiation-induced cancer, in particular breast cancer, for women. It will reduce the time it takes to manage patients with suspected PE in the emergency department, as patients that undergo thoracic imaging take an average of 4 h longer to treat than those who do not require it. Our study will thus have an indirect impact on other patients by limiting the overcrowding of emergency departments. Lastly, given the frequency of suspected pulmonary embolism in emergency departments and the very high usage rate of CT angiographies (80% in a recent observational study [10]), the SPEED&PEPS study should result in substantial savings in terms of the direct cost of diagnostic investigations and the indirect cost of hospitalizations due to waiting times or delayed harmful effects. We expect the cost per serious clinical event avoided in relation to the diagnostic approach to be very favorable compared to current practices.

